##### Case management

Case management is expected to improve quality of primary care for frail community-dwelling older people as well as delay or avoid institutionalization. The case manager in the FFF approach is expected to support the provision of proactive integrated care through a collaborative process of assessment, planning, facilitation, care coordination, evaluation, and advocacy for options and services to meet frail older patients’ needs [84]. The FFF approach uses home visits by case managers to achieve these goals. Furthermore, the case manager acts as a boundary spanner to ensure a well-functioning team of professionals supporting frail older patients.

##### Medication review

Older persons’ medicines are systematically and critically examined in a medication review. An important aspect of multidisciplinary consultation is the assessment of prescribed and over-the-counter medications used by these older people. The most recent overview of medications used by the older person, and experiences with medications, are discussed with the person (and informal caregivers or relatives). Possible additional actions include: (i) visitation of the older person by the elderly care physician to provide additional information about medications, (ii) the GP’s discussion of the person’s case history with the pharmacist, and (iii) the establishment of agreement about medication use between the GP and second-line medical care.

##### Self-management support

The FFF approach aims to improve self-management abilities and well-being among frail patients by incorporating different types of self-management support interventions, like skill building, educational materials, personal coaching, and the use of an individualized care plan. Needs and problems are listed by means of the so called SFSPC-model of reporting on Somatic, Functional, Social, Psychological, and Communicative indications for each individual frail older person. Subsequently, the individualized care plan is established and recorded, including the problems and needs, the formulated goals, and the possible actions and interventions. Agreements are made regarding follow-up and patients’ cases are evaluated at least once a year. Specific protocols for patient referral are established. For example, older persons are asked to identify preferred healthcare organizations and professionals (e.g. physiotherapists) in the fields of care and welfare. These preferred professionals are approached by the GP, elderly care physician or practice nurse. The professionals provide feedback information about patient care to the GP and/or elderly care physician.

##### Multidisciplinary teams

A strong team of professionals with different occupational backgrounds led by a GP is one of the core elements of the FFF approach in order to deliver high-quality care to frail elderly patients. Each case of an older person is discussed in multidisciplinary consultation. An inventory of relevant healthcare professionals is made by the GP and/or case manager and these professionals are invited to attend the consultation. They involve professionals in the care and treatment of patients (e.g. elderly care physician, physiotherapist, and psychologist) as well as professionals in the field of welfare when necessary. In the FFF approach, the elderly care physician plays an important role in the care process for older persons. Next to being present at the multidisciplinary consultations, the GP can obtain advice from the team’s elderly care physician on several complex health problems, e.g. depression and apathy, somatic or geriatric indications, and problem analysis in case of multimorbidity. The GP and the elderly care physician discuss whether one or several consultations are needed to assess each older person’s relevant healthcare needs. When necessary, other health and social care professionals (e.g. palliative care nurse) are involved. Plans and actions that are discussed during the multidisciplinary consultations are then discussed with the patient, tailored to the patient’s needs and wishes, and reported in the individualized care plan.

The interrelated key elements of the FFF approach are combined in a comprehensive approach to provide integrated primary care that can be tailored to the wishes and complex healthcare needs of frail community-living older people. The elements of the FFF approach are based on promising components of integrated care that were found in the literature [27–30]. As was explained in the previous section, we presume that this multicomponent approach influences the cognitions and behaviors of older patients and healthcare professionals which ultimately are expected to affect the productivity of patient-professional interactions and older patients’ well-being (See Fig. 1 and section ‘A theoretical model to facilitate the evaluation of integrated primary care approaches’).

## Methods

The second aim of our study is the development of a theory-guided study protocol to evaluate the innovative primary care approach FFF aimed at improving well-being among frail community-dwelling older people. We will explain the proposed methods to be used for our theory-guided evaluation of the FFF approach.

We aim to investigate (i) the potential effectiveness of the FFF approach in improving well-being among frail community-dwelling older people (*effect evaluation*), (ii) the implementation and context of the FFF approach in order to facilitate the interpretation of the results (*process evaluation*), and (iii) the cost-effectiveness of the FFF integrated primary care approach (*economic evaluation*).

### Study design

The longitudinal evaluation study has a mixed methods design in which a combination of quantitative and qualitative research methods are employed in order to evaluate the effectiveness, processes, and cost-effectiveness of the FFF approach. The evaluation study is performed between 2014 and 2017. The study has a matched quasi-experimental design with one pretest and one posttest measurement, i.e. the effects are measured before and after the intervention. Measurements are performed at baseline (T0) and 12 months thereafter (T1). Moreover, the study includes an intervention and a control group (i.e. intervention and control GP practices).

### Ethics approval

The research proposal has been reviewed by the medical ethics committee of the Erasmus Medical Centre in Rotterdam, the Netherlands (study protocol number MEC-2014-444). The committee decided that the rules laid down in the Medical Research Involving Human Subjects Act did not apply.

### Setting and GP practices

The study is performed in the western part of the Province of North Brabant in the Netherlands. This region contains a relatively high proportion of frail older persons compared with many other regions in the Netherlands [85]. GP practices in the region were eligible to participate in the intervention group of the study if they were not involved in other research projects and had implemented the FFF approach recently. Control GP practices were eligible for participation if GPs were not engaged in or planning to start screening older adults on frailty. In addition, GP practices that already follow-up older persons in a systematic way were not eligible to participate as control GP practices. Control GP practices continue to provide usual primary care and patients are able to use all available (primary care) services as before. We approached 17 GP practices for participation in this study (12 intervention practices and 5 control practices). In total, 11 of 12 GP practices that recently implemented the FFF approach agreed to participate in the study and 4 of 5 control GP practices consented to participate. The reasons for non-participation (2 GP practices) were the workload and time constraints. GP practices receive a small financial compensation for the administrative burden associated with the evaluation study.

### Participants and recruitment of frail older people for the FFF approach

The target population of the study consists of community-dwelling older persons aged 75 years and older registered at the 15 participating GP practices. With increasing age, the prevalence of frailty increases substantially [4, 86, 87]. Therefore, we decided to include persons aged 75 years and older. A four-stepped approach is used to describe the study population in terms of frailty, select patients that are eligible to participate in the FFF approach, include eligible patients in the evaluation study and match patients of intervention GP practices to patients in the control group (one-to-one matching).

***Step 1:*** Frailty is assessed among patients aged 75 years and older registered at the 15 participating GP practices. All older patients receive the validated TFI to screen for frailty [82]. Next to the TFI questionnaire, we provide a letter on behalf of the GPs and researchers, an information leaflet about the study, and a postage free return envelope. After 2-3 weeks, reminders are send to non-responders by mail and/or older patients are reminded by means of a telephone call. Older patients with a TFI score ≥ 5 are identified as frail [82]. The aim of this inventory is twofold, namely (i) to assess frailty in a community-dwelling population of older persons, and (ii) to arrive at frailty scores for the one-to-one matching procedure (Step 4) of patients that are selected and eligible to participate in the evaluation study.

***Step 2:*** The TFI frailty scores of older patients are handed over to the participating GPs in order to provide insight into their older patient population.

***Step 3:*** GPs of the intervention group make their own selection of eligible patients to be included in the FFF approach. This selection can be based on the frailty scores obtained by the administration of the self-report TFI questionnaire but can also be based on additional interviews and measures that are performed by the healthcare professional as part of the care provision. Although the TFI is a reliable and valid instrument for measuring frailty in community-living older adults [82, 88], the previously stated added value of other interviews and measures to assess frailty underlines the importance of not relying solely on the TFI as a measure to identify frail older patients [83]. Consequently, patients that are not frail according to the TFI (score ≤ 4) but are considered frail based on other examinations performed by healthcare professionals may nevertheless be selected for the FFF approach.

***Step 4:*** Eligibility of the frail older people selected in Step 3 is then assessed in terms of the inclusion and exclusion criteria by the researchers. For participation in the evaluation study we exclude (1) older people living in nursing homes or homes for the elderly, (2) persons having an estimated life expectancy of less than 3 months, and (3) people with an inadequate understanding of the Dutch language. A challenge in quasi-experimental designs is to reduce the risk of selection bias, i.e. preexisting differences in characteristics between the intervention group and control group due to the absence of random intervention assignment. This may result in a biased posttest measurement. In order to acquire unbiased estimates of the effects, the most important covariables should be balanced between intervention and control groups [89, 90]. To increase comparability of the intervention and control groups, we use one-to-one matching: each individual participant in the intervention group is matched to one participant in the control group with the same values of the key covariables, namely sex (male or female), frailty score (score on the TFI), and educational level (high or low). This one-to-one matching is performed by the researchers.

In total, 500 frail older patients are included (250 patients in the intervention group and 250 patients in the control group). Next to frail older patients, we include healthcare professionals in our evaluation study. All healthcare professionals involved in the healthcare delivery for older patients are approached to participate in our study. Our aim is to guarantee the inclusion of healthcare professionals with various backgrounds and areas of expertise, e.g. GPs, elderly care physicians, physiotherapists, case managers, practice nurses, and social workers. Moreover, we recruit professionals involved in the management of integrated care delivery. Approximately 60 professionals in the intervention group and 60 professionals in the control group are included.

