The proposed evaluation study has potential limitations and challenges. First, the absence of randomization makes the design more susceptible to bias [139]. Especially selection bias is a major concern in non-randomized studies. Systematic differences between the groups result in incomparable groups which ultimately may lead to biased estimates of the intervention effect [140]. To reduce the impact of this bias on the outcome measures studied, we aim to control for important factors in the analysis of the data and by means of matching [141]. To ensure that the intervention and control groups are similar for key covariables, we use one-to-one matching to balance groups instead of matching on a higher level (at healthcare practice level). Moreover, when necessary we use case-mix adjustments to take into account important dissimilarities. However, it is stated by Deeks and colleagues [140] that the degree to which techniques can sufficiently adjust for differences between the groups is still unclear, which ultimately provides no guarantee for unbiased study results [140]. In addition, unknown and unmeasured factors can still influence the outcome [142]. Second, the design of the study makes it impossible to blind participating healthcare professionals and frail older patients. Knowledge of the status of the person (receiving either the FFF approach or care as usual) may have an influence on the responses and may affect compliance [143]. Nevertheless, the interviewers that conduct the interviews with frail older persons are kept unaware of the group the person is in (intervention or control GP practice), so that the interviewers collecting outcome data are not influenced by that knowledge. Blinding of the interviewers aids to reduce differential outcome measurements (information bias) [143]. Due to the nature of the evaluation study, however, it is possible that the patient inadvertently reveals his or her status during the interview (e.g. disclosing information that is specific to the FFF approach). Third, one of the core challenges of the evaluation study is the willingness of frail community-dwelling older patients to participate in the study, especially in the long-term. Recruitment of appropriate numbers of patients requires a sufficiently long period [144]. We aim to optimize participation in the evaluation study by means of home visits instead of interviews over the telephone, recruiting interviewers that live in the same region as the older adults, and sending letters to older patients on behalf of their own GP. Fourth, although control GP practices continue to provide usual care, GPs in the control group may start initiatives to improve care delivery for frail older patients. We collect data on various interventions that are implemented to improve care for older adults and we monitor and describe the activities performed by the GPs. In contrast to the intervention GP practices, control practices are not supported financially by the health insurers to implement elements of the FFF approach. Fifth, recall bias may potentially affect our study findings. Earlier research using a 12 months period of asking patients about their healthcare visits show both under-reporting and over-reporting effects [145]. Administrative data could be included to accurately capture resources for an economic evaluation (if filled in correctly). Sixth, while we included patients and professionals in our theoretical framework and study protocol we did not include informal caregivers. Given their important role in supporting community-dwelling frail older people they are expected to influence the well-being of older persons as well. Given the complexity of the theoretical framework as presented in this paper we decided to first unravel the underlying mechanisms in the relationship between quality of care, cognitions and behaviors of patients and professionals and older persons’ well-being. Future research should look at the role of informal caregivers and their cognitions and behaviors as well. It may be easier to improve outcomes if the patient’s partner is a good self-manager with a positive frame of mind compared to a partner who is depressed, has low self-efficacy and poor investment behavior.

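### As written, recruitment Step 2 gives control GPs their patients' frailty scores before follow-up, so the comparator is usual care plus score feedback but is not described that way

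*Protocol article*

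**What the plan says.** All references are to the protocol article.

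- **Control practices** (Setting and GP practices): "Control GP practices were eligible for participation if GPs were not engaged in or planning to start screening older adults on frailty". During the study, "Control GP practices continue to provide usual primary care and patients are able to use all available (primary care) services as before". The practices are counted as follows: "11 of 12 GP practices that recently implemented the FFF approach agreed to participate in the study and 4 of 5 control GP practices consented", that is 11 + 4 = 15.
- **Step 1** (Participants and recruitment): "Frailty is assessed among patients aged 75 years and older registered at the 15 participating GP practices". The questionnaire is the Tilburg Frailty Indicator (TFI), and with it "we provide a letter on behalf of the GPs and researchers". Two aims are given: to assess frailty in this population, and to obtain scores for the one-to-one matching.
- **Step 2**, on what then happens to the results: "The TFI frailty scores of older patients are handed over to the participating GPs in order to provide insight into their older patient population". No arm is named here.
- **Step 3**, by contrast, names one arm: "GPs of the intervention group make their own selection of eligible patients to be included in the FFF approach". The selection may rest on the self-reported TFI scores, on other examinations, or both.
- **Step 4**: the researchers match on sex, TFI score and educational level.
- **Limitations** (Strengths and limitations): the contamination risk named is that "GPs in the control group may start initiatives to improve care delivery for frail older patients". The section adds that control-practice activities will be monitored and described, and that control practices have no insurer funding for FFF elements.

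**The concern.** Proactive case finding is the first of the five FFF components, and its named instrument is the TFI. The control-practice criterion exists to keep frailty screening out of the comparator. Under Step 2 as written, the study itself supplies control GPs with the result of such a screen.

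Two things are at stake. First, if control GPs act on the scores, some of the benefit of knowing who is frail reaches both arms, and the estimated difference is smaller than FFF against true usual care. Second, the Economic evaluation section charges case finding to FFF as an intervention cost, while control GPs receive part of its output without a matching cost. The limitations section looks only at what control GPs might start on their own and does not mention feedback from the study.

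**Working it through.** **Does Step 2 include control GPs?** The question is textual.

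1. In the same section, Step 1 uses the word participating for all 15 practices, hence for both arms.
2. Step 2 uses the same word for the GPs, with no restriction by arm.
3. Step 3 names the intervention group explicitly. When the authors mean one arm, they say so.
4. The section describes no withholding or delay for control scores.

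The natural reading is that control GPs receive the scores. Steps 1 and 2 come before selection and matching, so the hand-over precedes T1.

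**Is the hand-over needed in control practices?** Compare each stated use of the scores with who needs them.

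| Use of the TFI score | Who needs it | Must control GPs have it? |
|---|---|---|
| Describe frailty in the population (Step 1) | Researchers | No |
| One-to-one matching (Steps 1 and 4) | Researchers | No |
| Selection of patients for FFF (Step 3) | Intervention GPs | No |
| Insight for GPs into their own patients (Step 2) | GPs | Only for this purpose |

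Collecting control patients' scores is necessary, because matching uses the score. Passing them to control GPs serves neither the matching nor the delivery of FFF.

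**How much of FFF do controls receive?** FFF case finding consists of GP selection, a nurse home visit with the TFI, and further measures where needed. It leads on to case management, medication review, a care plan and multidisciplinary consultation. Controls receive a postal questionnaire and their GP receives a score. This is part of one component.

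**Effect on the ICER.** ICER = (cost with FFF − cost with usual care) / (effect with FFF − effect with usual care). If feedback helps controls, the denominator shrinks while the case-finding cost stays in the FFF term of the numerator, and FFF looks less favourable. Any extra care that control GPs then arrange raises the usual-care cost and pulls the other way. The ratio is distorted; its net shift cannot be read from the article.

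**Size.** The article gives no contamination rate. The following shows only how sensitive power is to assumed dilution.

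Inputs from the Sample size section: SD 0.45, difference 0.25 SD = 0.1125 points, two-sided alpha 0.05, beta 0.20, 400 of 500 patients expected at T1, so 200 per group.

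Plan's own figure: n per group = 2(z_alpha + z_beta)² / 0.25².

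- Two-sided: 2(1.960 + 0.842)² / 0.0625, giving 252.
- One-sided: 2(1.645 + 0.842)² / 0.0625, giving 198.

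The stated 198 matches a one-sided test. That mismatch is a separate matter, and low power at zero dilution is not due to the hand-over. Both starting points are shown.

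Power = Φ(d√(n/2) − z_alpha), with n = 200 and √(n/2) = 10:

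| Assumed dilution | d | Two-sided 0.05 | One-sided 0.05 |
|---|---|---|---|
| 0% | 0.250 | 0.705 | 0.804 |
| 10% | 0.225 | 0.614 | 0.727 |
| 20% | 0.200 | 0.516 | 0.639 |
| 30% | 0.175 | 0.417 | 0.542 |

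For example, at 20% dilution and two-sided: 0.200 × 10 − 1.960 = 0.04, and Φ(0.04) = 0.516. These figures ignore clustering and the planned baseline-using mixed and difference-in-differences models. They say nothing about which dilution is realistic.

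**The case against.** **The criterion is not breached.** A reader might infer that Steps 1 and 2 contradict the control-practice rule. They do not: it is an entry rule about what the GPs themselves do or plan, and a postal survey run for the study is outside its wording. What stands is the conflict with its purpose and with usual care as the comparator. The letter sent partly in the GPs' name makes that conflict more direct.

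**The comparator is still largely usual care.** A reader might infer that controls receive FFF case finding. The article supports only score feedback: no nurse visit, FFF selection or care pathway is given to controls. Practices already following up older persons systematically were excluded as controls, and control practices lack insurer funding for FFF elements. This limits the likely size.

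**Monitoring exists.** The Process evaluation section provides for in-depth study of control practices and structured interviews with the GPs of all practices, and the limitations section repeats the monitoring. This objection holds in part: monitoring can document what control GPs did, but it does not prevent contamination or change how the comparator is labelled.

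**No size can be claimed.** It is tempting to state a specific loss of power. No leakage rate appears in the article, so dilution is a likely direction and not a demonstrated fact.

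**Step 2 might have meant intervention GPs only.** That is possible, but the wording does not say so, and the repair would then be a single clarifying word.

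**Conclusion.** The point holds in a limited form. As Step 2 is written, control GPs receive before follow-up the same frailty information that intervention GPs may use for FFF selection, and no stated use in matching or delivery requires it. This conflicts with the purpose of the control-practice criterion and leaves the comparator inaccurately described. It does not invalidate the study.

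The likely direction is some dilution of the FFF versus usual-care contrast, with a distorted ICER because case finding is costed to FFF only. The size is unknown. The conclusion rests on two assumptions: that the word participating covers both arms in Step 2 as it does in Step 1, and that at least some control GPs would act on a score. The correction is worth making because it is cheap and determines what the result can be said to compare.

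**What to change.** Reconcile Step 2 with the control condition in Setting and GP practices, in one of two ways.

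1. **Restrict the hand-over.** State that Step 2 applies to intervention GPs, and that control patients' scores stay with the researchers until T1 data are collected. This is subject to the ethics arrangements and to what patients were told about sharing their scores; whether it is acceptable is for the investigators and the ethics committee. Cost: a sentence or two, a possible check of the patient information, and a later overview for control GPs.
2. **Describe what was done.** If control scores are or were shared, define the comparator as usual care plus frailty-score feedback. Use the planned GP interviews to record what control GPs did with the scores. State that the effect and the ICER do not capture any benefit of score feedback itself. That wording should not extend to case finding as a whole, since nurse visits, GP selection and further examination remain specific to FFF. Add the study's own feedback to the limitations. Cost: a few sentences, an added interview question and a slightly narrower claim.

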### Covariables

Several variables will be measured to provide insight into the characteristics of the study population and to facilitate interpretation of the outcomes of the evaluation study. Socio-demographic data (e.g. age, sex, marital status, educational level, net household income, and living situation) are collected during the interviews with frail older patients. We assess several additional variables in order to attempt to account for potential case-mix differences that may be introduced due to the non-random allocation of older patients to the intervention and control groups. Multimorbidity, physical functioning, cognitive functioning, and social functioning are assessed. Morbidity is assessed by indicating morbidities experienced in the past 12 months from a predefined list of 17 conditions (e.g. diabetes, chronic obstructive pulmonary disease (COPD), osteoporosis, and cancer). Multimorbidity is defined as the presence of two or more conditions from this list [103]. Physical functioning is assessed by means of a modified version of the Katz Activities of Daily Living index (Katz ADL index). Functional limitations are assessed for 8 activities in daily life, i.e. bathing, dressing, toileting, eating, continence, transfer, walking, shaving or to comb one’s hair [104, 105]. Additionally, cognitive functioning is assessed by means of the 12-item Mini-Mental State Examination (MMSE-12). The MMSE-12 focuses on cognitive aspects of mental functions and includes elements like orientation to time and place, recall of words, and complex commands, e.g. drawing a figure [106, 107]. Social functioning is assessed by means of the social component of the Dutch version of the 20-item Short Form Health Survey (SF-20) [108–110]. Next to the additional variables that are measured at the level of the older adults, we collect socio-demographic data of healthcare professionals (e.g. age, sex, educational level, occupation, and working hours).

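### One-to-one matching leaves age unbalanced by design, and the analysis does not commit to adjusting for it: an avoidable weakness, not a demonstrated bias

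*Protocol article*

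**What the plan says.** All references are to the protocol article.

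- **Participants and recruitment, opening paragraph.** Age sets the entry threshold: "With increasing age, the prevalence of frailty increases substantially", and on that ground "we decided to include persons aged 75 years and older". No upper limit is given.
- **Step 1.** "Frailty is assessed among patients aged 75 years and older registered at the 15 participating GP practices". The mailing therefore goes to people picked from practice registers by age.
- **Step 3.** "GPs of the intervention group make their own selection of eligible patients to be included in the FFF approach". The choice may rest on the TFI or on further interviews and measures, so it can include "patients that are not frail according to the TFI (score ≤ 4) but are considered frail based on other examinations". The section on proactive case finding adds that a GP's sense of alarm may start the selection. No comparable selection by control GPs is described.
- **Step 4.** The stated standard is that "the most important covariables should be balanced between intervention and control groups". The matching rule then requires a control "with the same values of the key covariables, namely sex (male or female), frailty score (score on the TFI), and educational level (high or low". There is no age variable, age band or caliper.
- **Covariables.** Age is recorded: "Socio-demographic data (e.g. age, sex, marital status, educational level, net household income, and living situation) are collected during the interviews with frail older patients".
- **Statistical analyses.** The effect is estimated by a difference in differences model within linear mixed modelling. Confounding is to be accounted for in general terms, and baseline differences are adjusted for if that proves necessary. Age is not named.
- **Strengths and limitations.** Selection bias is called a major concern. Matching and case-mix adjustment, when needed, are the remedies, and the article concedes that such adjustment cannot guarantee an unbiased result.

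**The concern.** The study is not randomised, so comparability depends on matching and on what the model adjusts for. Matching as written does nothing to bring the groups together on age beyond whatever follows from equal sex, TFI score and education. The two groups also enter by different routes: an FFF patient has passed a GP's clinical filter and, as far as the article says, a control has not. If age influences that filter at a given TFI score, the groups can differ in mean age after exact matching.

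What would be at stake is the 12-month change in SPF-IL, the primary outcome. Older people at the same TFI score might decline faster or leave the study more often. An age gap would then enter the estimated effect, and by the same route could reach costs and QALYs. Matching decides who enters, so it cannot be redone by an analysis plan after enrolment.

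**Working it through.** The plan states no figure for age balance, so there is none to reproduce. The check is of the logic.

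**1. What the rule permits.** Let the matching cell be sex × TFI score × education. The TFI runs from 0 to 15 (section on proactive case finding), so there are 2 × 16 × 2 = 64 cells. Within a cell the only shared age restriction is the lower limit of 75. A 90-year-old FFF patient and a 75-year-old control of the same sex, TFI score and education are a valid pair.

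**2. What difference in differences removes.** Write well-being of person i at time t (0 or 1) as

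Y = α + β·age + γ·t + δ·(age × t) + θ·(FFF × t) + group level + error.

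Subtracting T0 from T1 gives a change of γ + δ·age + θ·FFF. The term β·age cancels. The difference between the groups in mean change is

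θ + δ × (mean age FFF − mean age control).

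The unadjusted bias is therefore δ × (age gap). It is zero if there is no gap or if age does not affect the 12-month change (δ = 0). With complete data, an age main effect alone leaves the bias in place, because β has already cancelled. The age × time term is what removes it.

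**3. Can the design check δ or parallel trends?** The section on study design gives one pretest and one posttest. With a single pretest there is no earlier trend to compare between the groups.

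**4. Drop-out.** The section on sample size expects about 20% loss between T0 and T1, with death and refusal as examples. If loss depends on age and age differs between the groups, those with T1 data differ further. Multiple imputation deals with this only as far as age is in the models used.

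**5. Size.** The documents give no age gap and no value of δ. For scale only, assume a gap of 1 to 5 years and a δ of 0.005 to 0.02 SD of SPF-IL per year of age:

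| Assumed gap (years) | Assumed δ (SD per year) | Unadjusted bias (SD) | Share of the 0.25 SD target |
|---|---|---|---|
| 1 | 0.005 | 0.005 | 2% |
| 2 | 0.01 | 0.02 | 8% |
| 5 | 0.02 | 0.10 | 40% |

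The target is 0.25 × 0.45 = 0.1125 SPF-IL points (section on sample size). The width of this range shows that the documents do not fix the size. The sign depends on which group is older.

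**6. What a tie-breaker costs and achieves.** In a cell with f FFF patients and c available controls, exact matching yields min(f, c) pairs whichever controls are taken. Choosing by nearest age leaves that number unchanged. Where c is not larger than f, every control in the cell is used and there is little or no choice by age. The gain therefore comes from cells with spare controls. On average there are 250 / 64 ≈ 3.9 FFF patients per cell, and only four practices supply the controls, so a strict age caliper could cost pairs.

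**The case against.** The strongest defence is that the plan does deal with age, only not by matching. Age is collected, confounding is to be accounted for in the analysis, and residual bias is admitted. Exact matching on TFI score also removes the part of the age effect that runs through measured frailty, and frailty is the only reason the article gives for attending to age. Three exact variables, with other confounders left to regression, is a common and defensible trade-off when four practices must supply 250 controls.

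Most of this stands, and it limits the point. It does not remove it: selection goes beyond the TFI in one group only, and the promise to adjust is conditional and does not name age. A difference in differences model also needs age × time, not merely age.

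Three stronger readings are tempting and are not supported.

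- **FFF patients will be paired with much younger controls.** The rule permits such pairs. Nothing in the documents shows that they are typical or that FFF patients are the older group.
- **Wide age differences within pairs would themselves show bias.** With an assumed age SD of 5 years and no gap between the groups, two independent normal draws still differ by 2 × 5/√π ≈ 5.6 years on average. What matters in a group comparison is the gap between the group distributions, and simulating one largely returns the gap assumed.
- **Education is unknown when pairs are formed.** The section on covariables says it is collected at interview. It does not say that this is the only source, and the same list contains age and sex, which practices plausibly hold earlier.

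**Conclusion.** The point holds as an avoidable design weakness. Step 4 leaves age outside the balanced variables, the FFF group alone passes a GP filter that age could influence, and the analysis does not commit to the term that would remove an age-related difference in 12-month change.

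No bias is demonstrated. Its size and direction cannot be derived from the documents. The 2% to 40% of the target effect shown above rests wholly on assumed gaps and slopes, without adjustment. That an age effect on change remains at equal TFI score, sex and education is plausible, but the article does not state it. That practices know age before pairing is inferred from the mailing to registered patients aged 75 and over. Because age is measured, much of the problem can still be repaired in the analysis. Only the matching step has to be changed before enrolment.

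**What to change.** 1. **Matching rule (Step 4).** Keep exact matching on sex, TFI score and educational level. Where several controls qualify, choose the one nearest in age. This is one sentence and loses no pairs, since age only selects among exact matches.
2. **Reporting.** Give the age distribution by group, at T0 and among those measured at T1.
3. **Effect model.** Name age as a fixed covariate, with its interaction with time, regardless of the imbalance observed, and include age in the imputation model. This costs two model terms and no new data. It is needed as well as the tie-breaker, which closes only part of a gap when controls are scarce.

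If enrolment is already complete, items 2 and 3 remain available.
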